### Interview format

A semi-structured interview format will be used. Participants will be required to provide informed consent prior to interview. Conversation will be guided by a prompt guide of open-ended questions on topics such as diagnosis and treatment, and the effect the cancer and treatment had on participants’ lives, both at the time of treatment and at the time of the interviews. Therefore, whilst the interview will be conversational in nature, discussion will be directed towards identifying outcomes of importance to patients and carers. Towards the end of the interviews we will directly ask participants which outcomes they think are most important and should be measured in clinical trials. Key to this interview technique is that it allows participants to explain their experience of the illness and treatment in their own terms, and to raise and focus on the aspects of their journey that are most important to them.

### Interview analysis

In line with the principles of qualitative research, the analytical process will begin during data collection, as the data already gathered are analysed to inform the ongoing data collection. This will allow the study team to go back and refine questions, develop hypotheses, and pursue emerging avenues of inquiry in further depth in subsequent interviews [18].

We will take an interpretive approach, informed by the principles of the constant comparative method and by several procedural steps to ensure the quality of the analysis [19]. This involves an inductive process of identifying analytical categories as they emerge from the data (developing hypotheses from the ground or research field upwards rather defining them *a priori*). The analysis of patients’ and carers’ accounts will initially proceed in parallel, but related, courses. We shall analyse within each group for common themes, such as what is important to patients/carers, and how their lives have been affected by the cancer and treatment [20]. As the analysis develops we will compare across the different groups to identify convergences and divergences. We will examine how participants present their accounts as well as the content of the interviews. That is, we will not simply take participants’ accounts at face value.

We will compare data across the different groups (age, gender, sub-site, stage, HPV status, treatment modality, socio-economic status and length of time since treatment) and analyse for patterns in how these characteristics shape participants’ priorities following cancer treatment. As the principal investigator (PI), AW will lead a process of ‘cycling’ between the developing analysis and new data, and the complete team will develop and ‘test’ the analysis by periodic discussion of transcripts and reports on the developing analysis. Initially, each transcript will be read several times by AW before developing open codes to describe each relevant unit of meaning. Initial open coding will occur at multiple levels, from detailed descriptions of experiences line by line, to the general stance participants take towards different aspects of their lives. Through comparison within and across the transcripts the open codes will gradually be developed into theoretical categories and subcategories, to reflect and test the developing analysis.

The categories will be organised into a framework to code and index the transcripts using NVivo qualitative data analysis software (version 10, 2012; QSR International Pty Ltd, Victoria, Australia). The framework categories will be continually checked and modified to ensure an adequate ‘fit’ with the data, whilst also accounting for variant or exceptional cases. The categories and the assignment of data to them will be reviewed by a second member of the project team.

### The Delphi method

In order to gather opinion and to reduce the number of outcomes to a priority list for consideration in future OPSCC clinical trials we will use the Delphi method. This was originally developed by the RAND Corporation in the 1950s in order to forecast the influence of technology on warfare [21]. It is an iterative consensus technique which comprises sequential questionnaires answered anonymously by a panel of participants with relevant expertise [6].

Questioning takes place in rounds, and after each round of questions, an anonymous summary of the responses is fed back to the group. Individual participants may then decide to keep their original answers or to change their opinion in the subsequent round of voting. The advantage of this approach is that it is not face-to-face, and therefore avoids the problem of more vocal or apparently senior participants dominating the group discussion and therefore influencing others’ voting.

In general, the range of answers decreases and the group converges towards a consensus opinion over the course of several rounds. The process terminates after a pre-defined stop criterion, which for this study will be whichever occurs first: reduction of the long list of outcomes to ten or less; or on completion of the second round of voting.

## Synthesis of outcomes into Delphi questionnaire

### Outcomes from systematic review

The outcomes highlighted in the systematic review will be categorised under broader outcome domains, and presented in the questionnaire as such.

### Outcomes from interviews

Identifying measureable outcomes from the interview transcripts will be a more complex process. While some outcomes are likely to be obvious, the context must always be borne in mind, and it is important that our interpretation of the interview transcripts avoids either overlooking outcomes of importance to participants or misrepresenting them. For example, how extensively a participant talks about a particular aspect of their life is not necessarily indicative of its importance to them, since patients may talk about highly significant issues in a seemingly brief and casual manner as a way of managing their emotions. We will begin by analysing transcripts to identify experiences and priorities that map straightforwardly to obviously measurable outcomes. Examples include mouth dryness, difficulty swallowing and fatigue. Secondly, where a participant has described an experience or issue that was significant for them, the study team will attempt to map this to a measurable outcome. An example of this could be anxiety about survivorship clinic appointments, which is likely to be an expression of a patient’s anxieties about recurrence and survival. One researcher (AW) will be responsible for making these interpretations, and two researchers (AW and BY) will review a proportion of the outcomes and the supporting evidence from the interview transcript to scrutinise and ‘test’ the plausibility of the interpretations involved in translating participants’ accounts of their experiences and priorities into outcomes. Any uncertainties and a proportion of all outcomes derived through this process will be discussed with the whole study team (AW, [name], BY, [name]).

Patient interviews will be given primacy over the carer interviews in the analysis and derivation of outcomes. The carer acts as a witness to the patient’s experience and therefore their accounts will be used largely to illuminate our analysis of the patient accounts. For example, we will identify how far carers confirm or refute patient accounts; where divergences arise we will return to the patient accounts to identify the reasons for these or reconsider our interpretations as appropriate. The interview data will also be used to inform the presentation and labelling of outcomes, particularly for patients, in the Delphi study.

### Participants

The Delphi study will survey individuals with a stake in clinical trials for OPSCC. This includes OPSCC patients and their carers, and healthcare professionals involved in the management of patients with OPSCC, namely, medical and surgical oncologists, speech and language therapists (SLTs), and head and neck clinical nurse specialists (CNSs). It is important that a proportion of our clinician participants are also involved in research or clinical trials; therefore, we will recruit medical and surgical oncologists and SLTs from a list of those involved in a multicentre SCCHN trial that is ongoing and coordinated by our unit, and CNSs through personal contacts and professional bodies.

In the UK, patient and carer interviewees will be approached about participation in the Delphi study at the time of the interview. Additional patient and carer participants will be identified within survivorship clinics. The Delphi questionnaire will be included with a postal invitation, and a follow-up telephone call will be made 7 days following postage to confirm that the questionnaire was received. Clinician participants will be invited by email to participate in an online Delphi questionnaire and a reminder email will be sent after 7 days. The invitation will clearly state the importance of completing all rounds of the Delphi study. Attrition is more likely in participants with minority opinions and this can lead to an overestimation of the degree of consensus in the final results [6]. It will be clearly stated that outcomes important to that individual may not be included in the final core outcome set.

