### Statistical considerations

There are no recommendations for the number of participants to include in a Delphi study. In a systematic review by Sinha *et al*. of studies using the Delphi method in core outcome set development, the number of participants ranged from 13 to 222 [6]. We have a heterogeneous group of participants and therefore our sample size will need to be slightly larger to account for the likely diversity of opinions [24]. We aim to recruit around 30 patients and carers, and 30 clinicians, who will be medical and surgical oncologists, SLTs, and head and neck CNSs.

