#### ***Voting***

In other Delphi studies a ‘blank sheet’ round has been used to canvas participant opinion and generate a comprehensive and inclusive list of candidate outcomes. However, in conducting the systematic review and interviews we have effectively completed this process.

### Round 1

In round 1 of this Delphi study we will ask participants to rate each of the outcomes using the GRADE process, which suggests a 9-point scale (1 to 9) to rank their importance [23]. There will also be room for participants to add additional outcomes and to comment on why they have ranked outcomes as they have. Rankings of 7 to 9 indicate outcomes of critical importance, ratings of 4 to 6 represent outcomes that are important but not critical, while ratings of 1 to 3 are items that are deemed to be of limited importance. All outcomes will be carried through to the second round with first round scores displayed for each outcome. Consensus to carry an outcome through to the core outcome set will be defined as more than 70% of participants scoring its importance as 7 to 9 and less than 15% scoring it as 1 to 3. Additional outcomes will be coded by the study team using the same methods as for the interview and systematic review. Feedback will be analysed using software adapted from another Delphi study.

### Round 2

The number and percentage of participants that allocated each score will be presented to participants. However, feedback to each group will be randomised such that some participants receive only their group’s voting and others receive both groups’ voting. Participants will then be asked to rate the outcomes again, using the 9-point scale.

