### Analysis of voting

The opinions of different groups can be analysed either together or separately. Differences in opinion can be accounted for by having separate panels for different stakeholder groups [25]. It is not clear at this stage whether patients and carers will have different opinions to healthcare professionals. Macefield *et al*., in using a Delphi study to develop a core outcome set, demonstrated that the way in which feedback is delivered to participants affects the voting in subsequent rounds [26]. Feedback was randomised such that a proportion of both stakeholder groups received feedback from both stakeholder groups, and not just their own group. This altered voting, especially by the clinician group. We will randomise feedback such that half of the patient/carer group will receive results from the patients’/carers’ first round of voting, and half will receive results from patients/carers and clinicians. Similarly, half of the clinicians will receive results of the clinicians’ voting in the first round, and half will receive feedback from both patients/carers and clinicians. It is important to ensure that we have similar numbers between the panels for every round so that the final consensus is not numerically dominated by one group’s responses. As recommended by Sinha *et al*., we will report a measure of the distribution of scores for each outcome considered in the final round [6]. This is because cut-off scores, used in most studies, do not describe how strongly the minority feel, and so an apparent consensus could actually be masking major disagreement within the group [27].

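### The 70%/15% consensus rule does not say how people who miss round 2 are counted, although the protocol warns that such loss can overstate consensus

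*Protocol article*

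**What the plan says.** Under Participants in the Delphi part, the article states that "Attrition is more likely in participants with minority opinions and this can lead to an overestimation of the degree of consensus in the final results". Its response there is to encourage completion: "The invitation will clearly state the importance of completing all rounds of the Delphi study". Patients and carers also get a telephone call after 7 days to confirm receipt, and clinicians a reminder email after 7 days.

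The entry rule, under Voting (Round 1), is "more than 70% of participants scoring its importance as 7 to 9 and less than 15% scoring it as 1 to 3". The word used is participants; whether that means those recruited, those who voted in round 1 or those who voted in round 2 is not said. Also under Round 1: "All outcomes will be carried through to the second round with first round scores displayed for each outcome". The Delphi method section ends voting at whichever comes first: "reduction of the long list of outcomes to ten or less; or on completion of the second round of voting".

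Three other provisions bear on the point. Analysis of voting says "It is important to ensure that we have similar numbers between the panels for every round", and also that "we will report a measure of the distribution of scores for each outcome considered in the final round". Consensus meeting provides for a face-to-face meeting if consensus is not reached or the groups disagree significantly.

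**The concern.** The article names a bias and its direction: dissenters are the likelier ones to leave, so agreement can look stronger than it is. The rule that turns votes into a core outcome set takes no account of this. If only round-2 voters are counted, each dissenter who leaves shrinks the denominator without reducing the count of critical scores, and the percentage rises although nobody has been persuaded.

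At stake is which outcomes enter the set. An outcome admitted this way would look the same as one admitted through real convergence. The section on defining consensus says the definition must be fixed in advance so that it cannot favour the research team's views; a percentage with an open denominator falls short of that.

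**Working it through.** **Inputs**

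- Panel: "We aim to recruit around 30 patients and carers, and 30 clinicians" (Statistical considerations), so N is about 60.
- Rule: more than 70% scoring 7 to 9, and less than 15% scoring 1 to 3 (Voting).
- Drop-out between rounds: not given. Assumed range 5% to 30%.

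The article derives no attrition or sample-size figure, so there is none to reproduce.

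**The rule at N = 60.** 0.70 × 60 = 42, so at least 43 scores of 7 to 9 are needed. 0.15 × 60 = 9, so at most 8 scores of 1 to 3 are allowed.

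**Worked example, no score changed.** Round 1: 40/60 = 66.7% critical and 9/60 = 15.0% low. Both limits fail. One low scorer and two middle scorers (4 to 6) then miss round 2, a loss of 3/60 = 5%.

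- Round-2 voters only: 40/57 = 70.2% and 8/57 = 14.0%. Consensus.
- All 60, round-1 scores carried forward: 66.7% and 15.0%. No consensus.

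**Fewest non-critical drop-outs that create consensus**

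| Round 1: critical, low (of 60) | Drop-outs needed | Critical after | Low after |
|---|---|---|---|
| 42, 9 | 1 | 42/59 = 71.2% | 8/59 = 13.6% |
| 41, 9 | 2 | 41/58 = 70.7% | 8/58 = 13.8% |
| 40, 9 | 3 | 40/57 = 70.2% | 8/57 = 14.0% |
| 39, 9 | 5 | 39/55 = 70.9% | 8/55 = 14.5% |
| 38, 10 | 6 | 38/54 = 70.4% | 8/54 = 14.8% |
| 36, 12 | 9 | 36/51 = 70.6% | 7/51 = 13.7% |

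**How far below 70% an outcome can start and still pass the 70% limit.** Let d be overall drop-out and s the round-1 share scoring 7 to 9.

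- If all loss is from non-critical voters, s/(1 − d) must exceed 0.70, so s must exceed 0.70(1 − d).
- If non-critical voters are twice as likely to leave, critical voters leave at rate a = d/(2 − s), and s(1 − a)/(1 − d) must exceed 0.70.

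| Drop-out d | All loss non-critical | Twice as likely |
|---|---|---|
| 5% | 66.5% | about 69.2% |
| 10% | 63.0% | about 68.2% |
| 20% | 56.0% | about 65.9% |
| 30% | 49.0% | about 62.7% |

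**One case followed through at the 2:1 ratio.** Start at 40 critical and 10 low of 60. With p the drop-out rate among critical voters, 40p + 20(2p) = 80p people leave. Counts are expected values.

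- 10% (6 lost, p = 0.075): 37/54 = 68.5%, 8.5/54 = 15.7%. Fails.
- 15% (9 lost, p = 0.1125): 35.5/51 = 69.6%, 7.75/51 = 15.2%. Fails.
- 20% (12 lost, p = 0.15): 34/48 = 70.8%, 7/48 = 14.6%. Passes, narrowly.
- 30% (18 lost, p = 0.225): 31/42 = 73.8%, 5.5/42 = 13.1%. Passes.

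**Loss unrelated to opinion.** At 10% loss, 40/60 and 9/60 become 36/54 = 66.7% and 8.1/54 = 15.0%. Nothing changes.

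**The case against.** The strongest reply is that this is a condensed article, that handling of non-responders is commonly left to a fuller document, and that noting a risk while working for retention is coherent. It is true that a fuller protocol or analysis plan may settle the matter. But the article itself states the bias and the thresholds, and asks for the definition to be fixed beforehand; the thresholds as printed do not fit the warning.

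Several stronger readings are tempting and not supported:

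- *That the plan counts only final-round voters.* It does not say so. That is the natural reading of a rule applied to a re-rating, but it is an inference. In the sentence on score distributions, the final round describes the outcomes, not who is counted.
- *That drop-out does inflate consensus.* The text says it can. The effect needs loss related to opinion and, unless that loss is heavy or strongly one-sided, an outcome near the threshold.
- *That the invitation wording is the only response.* There are also the call, the reminder email, the distribution reporting and the conditional meeting. These are real, but they do not close the gap. The contacts aim to raise response and cannot correct loss that occurs. A final-round distribution, read naturally, also omits those who left. A false consensus does not by itself trigger the meeting.
- *That drop-out unbalances the panels.* The article asks for similar panel numbers at every round, and the calculations above contain no panels, so this is not claimed.
- *That every drop-out has a round-1 score on every outcome.* Participants may add outcomes in round 1; nobody has a round-1 score for those, and items may be left blank.

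One more objection stands: carrying a score forward assumes that the person would have ignored the feedback, whereas the Delphi method invites people to revise. That rules it out as the primary rule but not as a check.

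**Conclusion.** The point holds in limited form. The denominator of the 70%/15% rule is undefined for people who miss round 2, and the article states no check for a bias that it acknowledges. If round-2 voters are counted, one to three non-critical drop-outs out of 60 are enough to admit an outcome that started at 40 to 42 critical scores with 9 low ones. With a 2:1 drop-out ratio the reach is modest: at 10% loss only outcomes already at about 68% or more can pass, and at 20% those at about 66% or more. All of this rests on assumed drop-out rates and on loss related to opinion. It shows what the rule permits and does not forecast what will happen. It is worth correcting because it is cheap and the trial status section says Delphi recruitment is still being prepared.

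**What to change.** 1. State that the primary rule uses round-2 voters.
2. Tabulate, by panel, the round-1 scores of those who completed round 2 against those who did not.
3. For outcomes rated in round 1, repeat the rule as a sensitivity analysis with non-completers' round-1 scores carried forward. Outcomes added by participants are outside this check.
4. Flag any outcome that meets the rule only among round-2 voters and take it to the consensus meeting already provided for, adding this as a reason to discuss an outcome there.

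The cost is a few sentences of analysis text and two tables from scores that round 1 collects anyway. The downside is that a few borderline outcomes need discussion before entry, and the meeting gains a trigger it does not now have.

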### Definition of consensus

This must be defined upfront to avoid consensus being defined in a way that could bias the results towards the beliefs of the research team. For an outcome to be included in the core outcome set there must be majority agreement of the critical importance of an outcome, and minority agreement that the outcome is not important. Conversely, for an outcome to be excluded there must be majority agreement that the outcome is not important, and only minority agreement that it is critically important. These judgements are based on GRADE Working Group recommendations and are discussed in further detail below [22,23].

### Statistical considerations

There are no recommendations for the number of participants to include in a Delphi study. In a systematic review by Sinha *et al*. of studies using the Delphi method in core outcome set development, the number of participants ranged from 13 to 222 [6]. We have a heterogeneous group of participants and therefore our sample size will need to be slightly larger to account for the likely diversity of opinions [24]. We aim to recruit around 30 patients and carers, and 30 clinicians, who will be medical and surgical oncologists, SLTs, and head and neck CNSs.

#### ***Voting***

In other Delphi studies a ‘blank sheet’ round has been used to canvas participant opinion and generate a comprehensive and inclusive list of candidate outcomes. However, in conducting the systematic review and interviews we have effectively completed this process.

### Round 1

In round 1 of this Delphi study we will ask participants to rate each of the outcomes using the GRADE process, which suggests a 9-point scale (1 to 9) to rank their importance [23]. There will also be room for participants to add additional outcomes and to comment on why they have ranked outcomes as they have. Rankings of 7 to 9 indicate outcomes of critical importance, ratings of 4 to 6 represent outcomes that are important but not critical, while ratings of 1 to 3 are items that are deemed to be of limited importance. All outcomes will be carried through to the second round with first round scores displayed for each outcome. Consensus to carry an outcome through to the core outcome set will be defined as more than 70% of participants scoring its importance as 7 to 9 and less than 15% scoring it as 1 to 3. Additional outcomes will be coded by the study team using the same methods as for the interview and systematic review. Feedback will be analysed using software adapted from another Delphi study.

### Round 2

The number and percentage of participants that allocated each score will be presented to participants. However, feedback to each group will be randomised such that some participants receive only their group’s voting and others receive both groups’ voting. Participants will then be asked to rate the outcomes again, using the 9-point scale.

